##### Pulmonary function and respiratory muscle strength

1.4.4.1

The PFTs will be measured using a Vitalograph 6800 PFT spirometer (Vitalograph Inc, USA) and the decision whether to use the mouthpiece with nasal clip or the mask will be based on the evaluation of each single patient, specifically on the presence of facial muscle weakness. The PFTs that will be included are the FVC and SVC, which will be performed in both and supine positions; they are expressed both as absolute value, in FVC% and SVC%, respectively) [14]. The patient is guided to inhale deeply and, subsequently, to expire as fast as far they could.

Maximal inspiratory (MIP), and maximal expiratory pressure (MEP) were measured as previously described by Black & Hyatt [15]. Sniff nasal inspiratory pressure (SNIP) will be measured at functional residual capacity as previously described [16]. The highest value from three or more attempts will be selected for analyses and standardized to predicted percentages of Brazilian population [17].

##### Peak cough flow (PCF) and assisted PCF

1.4.4.2

The maneuver, expressed in L/min, will be performed with a mask of fitting size, with a seated patient who is asked to inhale as much air as possible and then cough it out. At least three acceptable and repeatable trials were performed, and the best out of these maneuvers will be chosen.

PCF and manually assisted PCF by LIC will be measured using a sealed oronasal mask with a handheld portable peak flow meter (Respironics INC. USA), which recent guidelines recommend for measuring expiratory flow rates during voluntary cough [18].

##### Bulbar function

1.4.4.3

Bulbar function will be assessed using the three components of the revised ALS functional rating scale (ALSFRS-R) relevant to bulbar function (i.e. speech, salivation and swallowing, each scored on a scale of 0–4).

##### Secondary outcomes

1.4.4.4

Data on blood gases will be collected to assess PaCO_2_ levels at baseline. The Amyotrophic Lateral Sclerosis Functional Rating Scale revised score (ALSFR-r), site of onset [bulbar(B) versus non-bulbar (NB)], time elapsed (months) between symptom onset and ALS diagnosis, months elapsed from diagnosis to noninvasive ventilation (NIV) prescription will also be collected. Voice parameters will be assessed by Maximum Phonation Time and its acoustic analysis.

The Functional Oral Intake Scale (FOIS) [19] will be used as an index of daily oral intake. This validated 7-point ordinal scale measures what foods an individual consumes to meet their daily nutritional and hydration requirements and ranges from a 1 (nothing by mouth) to 7 (full oral diet with no restrictions). The Eating Assessment Tool-10 (EAT-10)was administered as a patient reported outcome (PRO) of swallowing function [20]. The EAT-10 is a validated 10-item patient rated questionnaire with each question rated on a 5-point ordinal scale. A total EAT-10 score ranges from 0 (indicative of no self-perceived swallowing impairments) to 40 (indicative of severe swallowing impairments).

### Sample size calculation

1.5

This study is powered to detect a clinical meaningful difference in decline rate of pulmonary function (% predicted FVC). Based on meta-analysis conducted by Silva et al. [21], the minimal clinical important difference (MCID) from baseline to 1 year is 2–6%, 16 participants for each arm will need to be recruited with 80% power at two-tailed 5% level of significance. After take into account 30% attrition, a total sample size of 42 participants is required.

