**Methods:**

This parallel-group, assessor-blinded randomized controlled trial, powered for superiority, aims to assess pulmonary function, respiratory muscle strength, peak cough flow as primary outcomes. Forty-two participants are being recruited referral neuromuscular disease center at Brasilia, Brazil. Following baseline testing, participants are randomized using concealed allocation, to receive either: a) breath stacking technique alone or b) breath stacking technique plus EMT.

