### Methods/design

1.1

This two-arm, parallel (1:1), superiority, blinded-assessor, randomized controlled trial is being conducted at referral neuromuscular disease center in Brasilia, Brazil. This trial has been prospectively registered on Clinical Trials Registry (NCT04226144). Recruitment commenced in August 2019.

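### The total of 42 does not cover the stated 30% attrition: about 29 patients would complete, against the 32 on which the 80% power rests

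*Protocol article*

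**What the plan says.** Section 1.5 of the protocol article makes two linked statements. The first gives the number needed for power: "16 participants for each arm will need to be recruited with 80% power at two-tailed 5% level of significance". The second inflates it: "After take into account 30% attrition, a total sample size of 42 participants is required". The Methods paragraph of the abstract repeats the total: "Forty-two participants are being recruited referral neuromuscular disease center at Brasilia, Brazil". Section 1.1 (Methods/design) gives the allocation as 1:1, so 42 means 21 per arm. The article does not print the formula that leads from 32 to 42.

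Two other places bear on who counts as lost. Section 1.2 (Participants) keeps data gathered before a patient withdraws. Section 1.6 (Statistical analysis) computes each patient's decline rate up to that patient's last evaluation and compares the arms with an unpaired t-test.

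**The concern.** Attrition is a share of the patients enrolled. To have 32 left after losing 30%, the required number must be divided by the retained fraction, 0.70. Adding 30% to 32 gives a smaller number, and 42 is what that addition produces. If 42 was reached that way, the trial cannot have both the power and the attrition allowance that it states. This section is the article's only justification of the sample size, so a reader would credit the trial with a power that its own figures do not deliver.

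**Working it through.** **Inputs, all from section 1.5 unless noted**
- Patients needed: 16 per arm, 32 in total
- Power 80%, two-sided 5% level
- Attrition 30%
- Stated total 42 (also in the abstract), allocated 1:1 (section 1.1)
- Test: unpaired t-test (section 1.6)

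**Step 1. Reproduce the stated total.**
- Adding 30%: 32 × (1 + 0.30) = 41.6, rounded up to 42.
- Per arm: 16 × 1.30 = 20.8, rounded up to 21, and 2 × 21 = 42.
- Both routes give the printed figure.

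**Step 2. Total needed if 30% of those enrolled are lost.**
- 32 / (1 − 0.30) = 45.7, rounded up to 46.
- Per arm: 16 / 0.70 = 22.9, rounded up to 23, and 2 × 23 = 46.
- Check: 46 × 0.70 = 32.2, so 32 remain.

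**Step 3. What 42 delivers.**
- Remaining after 30% loss: 42 × 0.70 = 29.4, or 14.7 per arm.
- Shortfall against 32: about 3 patients.
- Attrition that 42 can absorb: 1 − 32/42 = 23.8%.

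**Step 4. Cost in power.** The section gives no standard deviation and only a range of 2–6% for the effect, so the 16 per arm cannot be rebuilt from its inputs. The loss can still be measured relative to it. With a two-sample t-test at two-sided 5%, 16 per arm has 80% power for a standardised difference of 1.024. Holding that difference fixed:

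| Patients analysed | Power |
|---|---|
| 16 per arm | 80.0% |
| 15 per arm | 77.2% |
| 14.7 per arm | 76.3% |
| 15 and 14 | 75.7% |
| 14 per arm | 74.1% |

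The normal approximation (standardised difference 0.99) gives 76.0% at 14.5 per arm, so the method hardly matters. The standardised difference detectable with 80% power rises from 1.02 to 1.07 at 14.7 per arm. The type II error rises from 20% to about 24%.

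**The case against.** The strongest objection is that a patient lost to attrition is not always lost to the analysis. Data before withdrawal are kept, and the decline rate runs to the last evaluation, so anyone seen at week 8 or later yields a value. Of the 12.6 patients expected to be lost (42 − 29.4), about three reaching week 8 would bring the number of decline rates back to 32. This stands in part: 29 is safely a count of completers, and the number analysed could be higher. It does not rescue the calculation. Section 1.5 treats the 30% as loss to be made up by extra recruitment. A patient lost before week 8 has no decline rate at all, and rates over a shorter interval are likely to be less precise. If partial follow-up was meant to count, the 30% is misdescribed and still needs restating.

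Three smaller points can be made:
- **The multiplication by 1.3 is inferred.** No formula is shown. This is true, but 70% of 42 is below 32 however 42 was reached.
- **The power figures depend on an unverified 16 per arm.** This is also true. They measure a loss relative to the plan's own base and are not an independent estimate of the trial's power.
- **The effect is small.** It causes no bias, leaves the type I error unchanged, and disappears if attrition stays at or below about 24%. All of this stands and bears on how serious the error is, not on whether it exists.

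**Conclusion.** The concern holds. With 42 randomised, 80% power and 30% attrition cannot both be true on the plan's own figures. The allowance falls four patients short (46 against 42). At 30% loss, about 29 patients complete and power is about 76%, within 74% to 77% for 14 to 15 per arm. This rests on two assumptions: that 16 per arm gives 80% power, as the plan says, and that the 30% are lost to the analysis, as the sample size section implies. The error is modest in size, but it is a wrong statement in the article and is easily corrected.

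**What to change.** Restate the last sentence of section 1.5, for example: 42 randomised patients allow for about 24% attrition at the planned 80% power; at 30% attrition about 29 patients complete and power is about 76%, taking 16 per arm as the number that gives 80%. This costs one sentence and no extra patients.

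If the sponsor prefers to keep 80% power with 30% attrition, the target becomes 46 (23 per arm), four more patients, and the abstract must change to match. The article describes the trial as still recruiting, so this was open when it was written.

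With either choice, show the inflation as division by one minus the attrition rate, and say whether patients with partial follow-up count towards the 30%.

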### Statistical analysis

1.6

Baseline characteristics will be summarized, including age, sex, time of diagnosis, onset of symptoms local, drugs, primary and secondary outcomes, and imbalances will be investigated.

For each variable, the Shapiro Wilk test will be used to evaluate the normality of the distribution and the Levene test will be performed to evaluate the homogeneity of variance. The differences between groups will be analyzed by the unpaired *t*-test and for continuous variables and chi-square test for categorical variables. The decline rate will be calculated as the difference between baseline and final observation, dividing the result by the number of months between baseline and last evaluation. Spearman test will be used to evaluate the longitudinal decline correlations between pulmonary function tests and both bulbar impairment and disease progression rate.

Exploratory analysis of 2-year survival will include descriptive Kaplan-Mayer survival curves and cox regression with treatment intent.

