Expiratory muscle training (EMT) has been investigated as a new effective tool to enhance maximal PCF in individuals with neuromuscular diseases. This technique aims to improve subglottic air pressure generation, swallowing and airway clearance [10]. Reyes et al. have shown that EMT plus breath stacking improved voluntary and reflex cough in Parkinson disease [11]. Plowman et al. have demonstrated that 5-week EMT training was feasible and led to improvements in respiratory and bulbar function in ALS patients [10,12]. However, both studies have not used the techniques together, which may improve the clinical results. Of note, the randomized controlled trials performed in ALS patients have not investigated the addiction of EMT together breath stacking in this population.

This trial aims to determine if breath stacking plus EMT is more effective than breath stacking alone to decrease the decline rate on the inspiratory/expiratory muscle strength, pulmonary function testing and voluntary PCF in ALS patients. We hypothesize that those receiving breath stacking plus EMT will have a slower decline in these parameters from baseline to 6 months, compared to patients that receiving breath stacking alone. The key secondary outcomes are to assess whether EMT plus breath stacking is superior to breath stacking alone to swallowing function and ability to speech. This protocol is reported according to the Standard Protocol Items: Recommendations for interventional Trials (SPIRIT guidance) [13].

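### Section 1.6 allows only a t-test or a chi-square test between arms, so the 7-level ordinal FOIS has no suitable method and its test is left open

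*Protocol article*

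**What the plan says.** - Section 1.6 sets one rule for comparing the arms: an unpaired t-test for continuous outcomes and a "chi-square test for categorical variables". Shapiro-Wilk and Levene tests are to be run on each variable, but no other between-group test is named if they fail. The only rank method is Spearman's, and it is reserved for correlations.
- Section 1.4.4.4 describes FOIS as follows: "This validated 7-point ordinal scale measures what foods an individual consumes". It runs from 1 to 7. The same section gives EAT-10, a 0 to 40 total, as the patient-reported measure of swallowing function.
- The Introduction states the aim: "The key secondary outcomes are to assess whether EMT plus breath stacking is superior to breath stacking alone to swallowing function". The sentence goes on to speech and names no instrument.
- Section 1.5 sizes the trial on % predicted FVC, not on FOIS: "16 participants for each arm will need to be recruited", with "80% power at two-tailed 5% level of significance", and then "After take into account 30% attrition, a total sample size of 42 participants is required".

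**The concern.** The article declares a data type that its own test rule does not cover. Anyone following section 1.6 must treat FOIS either as nominal or as an interval measurement.

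A chi-square test on a 2 x 7 table would give the same result if the seven levels were shuffled. It spreads up to 6 degrees of freedom over at most 42 patients and does not use the direction of a shift. A t-test keeps the order but reports a mean difference that counts each one-level step as equal.

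The choice between the two is open until someone makes it, possibly with data in hand, and it can matter a good deal for a measure that informs a key secondary question.

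**Working it through.** **Inputs from the article.** Two arms, 1:1 (section 1.1); 42 patients, so 42 / 2 = 21 per arm; 16 evaluable per arm; two-sided 5% level (section 1.5); FOIS levels 1 to 7 (section 1.4.4.4). The total of 42 reproduces as 32 x 1.3 = 41.6, rounded up. No power is stated for FOIS, so there is no planned figure to reproduce for it.

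**Inputs assumed.** The article gives no FOIS distribution and no FOIS effect. Four control-arm shapes were used (probabilities for levels 1 to 7):
- uniform: 1/7 each
- centred: .05, .10, .20, .30, .20, .10, .05
- skewed to 7: .03, .03, .04, .10, .20, .25, .35
- ceiling: .02, .02, .03, .05, .10, .18, .60

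The treatment effect is a common odds ratio (OR): odds(Y ≤ k, experimental) = odds(Y ≤ k, control) / OR for every k, with OR = 1, 3, 5 and 8.

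**Sparse cells.** A 2 x 7 table has 14 cells: 42 / 14 = 3.0 patients per cell on average, and 32 / 14 = 2.3 at 16 per arm. With equal arms the expected count is half the column total, so an expected count of 5 needs 10 patients at that level. With 42 patients, at most four of the seven levels can reach that.

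**Power.** 3,000 simulated trials per setting, comparing Pearson chi-square (empty columns dropped), the tie-corrected Wilcoxon-Mann-Whitney test and the unpaired t-test. Results at 21 per arm:

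| Shape | OR | Chi-square | Rank test | t-test | Chi-square / rank |
|---|---|---|---|---|---|
| Uniform | 3 | 21.8% | 49.1% | 49.4% | 0.44 |
| Uniform | 5 | 47.4% | 81.1% | 80.4% | 0.58 |
| Uniform | 8 | 73.2% | 95.5% | 94.5% | 0.77 |
| Centred | 3 | 19.1% | 48.9% | 48.6% | 0.39 |
| Centred | 5 | 44.2% | 80.1% | 79.7% | 0.55 |
| Centred | 8 | 72.7% | 94.5% | 94.5% | 0.77 |
| Skewed | 3 | 20.9% | 46.8% | 41.8% | 0.45 |
| Skewed | 5 | 41.2% | 75.6% | 69.1% | 0.55 |
| Skewed | 8 | 64.0% | 91.5% | 84.4% | 0.70 |
| Ceiling | 3 | 12.6% | 35.3% | 29.7% | 0.36 |
| Ceiling | 5 | 21.5% | 57.6% | 48.0% | 0.37 |
| Ceiling | 8 | 34.1% | 74.0% | 62.9% | 0.46 |

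- Chi-square against the rank test: the ratio runs from 0.36 to 0.77, a loss of 23 to 64%. At OR 3 to 5 it is 0.36 to 0.58. At 16 per arm it is 0.29 to 0.63, a loss of 37 to 71%.
- t-test against the rank test: at OR 5 the gap is 81.1 - 80.4 = 0.7 points (uniform), 0.4 (centred), 6.5 (skewed) and 57.6 - 48.0 = 9.6 (ceiling). The largest gap in the table is 74.0 - 62.9 = 11.1 points.
- Chi-square against the t-test at OR 5: the choice of branch moves power by 26.5 points (48.0 - 21.5, ceiling) to 35.5 points (79.7 - 44.2, centred).
- Type I error of chi-square (OR = 1): 2.0 to 4.0% at 21 per arm and 1.6 to 3.8% at 16 per arm, against a nominal 5%.

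**Cross-check without simulation.** Take the non-centrality that gives a 1-df test 80% power: (1.960 + 0.842)² = 7.85. On 6 df the same non-centrality gives 52%. Starting from 50% power (1.960² = 3.84), 6 df gives 26%.

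**The case against.** **The article never assigns FOIS to chi-square.** This stands. Section 1.6 also has obvious categorical variables in view, such as sex and site of onset. A reader might infer that the plan will halve the power for FOIS. The text does not support that: the loss arises on one of two readings, and on the other it is small.

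**FOIS is not the swallowing outcome on its own.** This also stands. The aim names no instrument and includes speech, FOIS is introduced as an index of oral intake, and EAT-10 is the measure labelled swallowing function. EAT-10 would naturally go to the t-test. So it does not follow that a real swallowing benefit would be missed through the choice of test alone.

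**The bulbar score.** The three-item ALSFRS-R sum (0 to 12) might seem open to the same criticism. It is unlikely to be tabulated as nominal, section 1.6 already plans a rank correlation with bulbar impairment, and no loss was computed for it. It is not part of this point.

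**The magnitude rests on assumed inputs.** True, hence a range. The direction was the same in every non-null scenario. A conservative type I error also means no added false-positive risk.

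**Test assignment belongs in the analysis plan.** This holds only in part. An unseen analysis plan may settle the matter, but the article does not stay silent: it fixes a two-branch rule, and neither branch suits an outcome it calls ordinal.

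**Conclusion.** The point holds in conditional form. Section 1.6 has no suitable between-group method for an outcome that section 1.4.4.4 declares ordinal, and it does not say which of its two tests FOIS receives.

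- If chi-square: power is roughly a quarter to two thirds lower than with a rank test at 21 per arm, about half lower for moderate effects (OR 3 to 5), with sparse cells and a conservative test.
- If the t-test: the loss is 0 to about 10 points (11 in the most extreme scenario run), largest with a ceiling, and the estimate assumes equal spacing.

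These figures depend on the four assumed FOIS shapes and on proportional odds; the article supplies neither. A reader might go further and conclude that the trial's main result is at risk. It is not: the sample size is set on % predicted FVC, and the primary outcomes do not depend on how FOIS is tested. The defect concerns one secondary measure. It is worth correcting because a better method than either stated test is available at almost no cost.

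**What to change.** In section 1.6, add that FOIS at 24 weeks is compared between arms with a Wilcoxon-Mann-Whitney test stratified by the bulbar stratum used in the randomisation, reported as a probability of superiority with 95% CI.

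A proportional-odds model adjusted for baseline FOIS and stratum, reported as a common odds ratio with 95% CI, is an alternative if the data support it. With seven levels it needs six intercepts plus terms for arm, baseline and stratum: 6 + 3 = 9 parameters if baseline enters as one linear term. That is many for 42 patients or fewer, so the stratified rank test is the safer default. The choice should be fixed before unblinded data are seen.

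Restrict chi-square, or Fisher's exact test where cells are small, to nominal variables.

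Cost: one sentence, with no new data and no extra patients. The article describes the trial as still recruiting, so the change can precede the analysis.

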### Randomization and allocation

1.3

Following informed consent and all baseline assessments, participants will be randomized 1:1 to either the intervention group (EMT plus breath stacking) or the control group (breath stacking alone-usual care). A stratified block permutation randomization will be used with bulbar and non-bulbar onset symptoms as the stratification factors, to ensure balance between the groups. The patients will be dichotomized into normal to moderate bulbar impairment (score 7–12) and severe bulbar impairment (score 0–6).

The randomization schedule was prepared by a researcher independent of the trial.

The trial is being conducted in accordance with theDeclaration of Helsinki and was approved by the Fundação de Ensino e Pesquisa em Ciências da Saúde (FEPECS) Ethics Committee and received approval 6/18/2019 (Document number 3400412).

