## Discussion

2

This study will assess the impact of expiratory muscle training associated with breath stacking technique on pulmonary function, respiratory muscle strength, peak cough flow and functional assessment in ALS patients. We chose the pulmonary function parameters and cough efficacy as primary outcomes because they plays a critical role in predicting the prognosis of these patients, both in terms of survival and functional ability [22].

A recent study suggests that expiratory muscle training was feasible and well-tolerated in ALS patients, and led to improvements of expiratory muscle strength and swallowing kinematics [10]. However, no differences were noted for FVC. The breath stacking technique can increase inspired volumes that lead to greater peak cough flow, allowing for improvements in mucus clearance and reduction in atelectasis (6). We believe that the increase of inspired volume may increase the efficacy of expiratory muscle training in the ALS population.

The American Academy of Neurology, Practice Parameters has recommended that breath stacking technique as a respiratory aid in patients with neuromuscular diseases. This trial aims to determine the impact of an inspiratory and expiratory synergist program in ALS patients using the same resuscitation bag with an addiction of a new valve (VUP) that allows for increased lung capacity and the addiction of a submaximal load to expiratory muscles during the expiration phase, which may provide muscular conditioning in ALS patients and contribute to a maintained bulbar function.

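### The planned Spearman correlations take no account of randomised arm, so a pooled coefficient would absorb any treatment effect that reaches both variables of a pair

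*Protocol article*

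**What the plan says.** Section 1.6 of the protocol article gives the correlation analysis in one sentence: "Spearman test will be used to evaluate the longitudinal decline correlations between pulmonary function tests and both bulbar impairment and disease progression rate". It names no arm, stratification or adjustment, and it does not say in words that the arms are pooled. The treatment comparison is a separate statement: "The differences between groups will be analyzed by the unpaired" *t*-test, with chi-square for categorical variables.

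The same section defines the pulmonary variable: "The decline rate will be calculated as the difference between baseline and final observation", divided by the months between the two. It is therefore a post-randomisation quantity.

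On what EMT is expected to do, the article says:

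- **Pulmonary side (Introduction):** "We hypothesize that those receiving breath stacking plus EMT will have a slower decline in these parameters from baseline to 6 months". The parameters meant are respiratory muscle strength, pulmonary function and cough flow.
- **Bulbar side (Introduction):** the key secondary question is whether the combination is "superior to breath stacking alone to swallowing function and ability to speech".
- **Bulbar side (Discussion):** the added expiratory load is described as one "which may provide muscular conditioning in ALS patients and contribute to a maintained bulbar function".
- **Bulbar measure (section 1.4.4.3):** "Bulbar function will be assessed using the three components of the revised ALS functional rating scale (ALSFRS-R) relevant to bulbar function", that is, speech, salivation and swallowing.

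The article does not say whether bulbar impairment in the correlation is a baseline score or a change, and it does not define disease progression rate.

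**The concern.** A Spearman coefficient computed over two randomised arms mixes two things: how the variables move together among patients treated alike, and how far apart the arms lie on both variables. Only the first describes the link between respiratory and bulbar decline in ALS. If EMT slows both, patients in the EMT arm tend to sit low on both declines and control patients high on both. A positive coefficient then appears even if the two declines are unrelated within each arm.

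For pulmonary and bulbar decline, a shift on both sides is an outcome that the trial sets out to test: swallowing and speech are key secondary outcomes and two of the three bulbar items. A plain Spearman test has no term for arm and cannot separate the two components. At stake is the interpretation of a secondary correlation and its p-value.

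**Working it through.** **Plan's own figure.** The article gives no figure for the correlation analysis, so there is none to reproduce. The Sample size calculation section (1.5) gives 16 per arm, 80% power, two-sided 5%, and 42 patients in total. These supply a scale for the shifts and two sample sizes to examine (32 and 42).

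**Scale of the shift.** No SD is stated, so only the standardised effect can be recovered:

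d = (1.960 + 0.842) × √(2/16) = 2.802 × 0.3536 = 0.99 (normal approximation); the *t*-based value is 1.02.

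A shift of about 1 SD is thus the effect that the trial is sized to detect on FVC. Nothing in the article supplies a shift for bulbar or functional measures, so those below are assumptions shown over a range.

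**Formula.** Take 1:1 arms, within-arm SD of 1 for both variables, arm shifts d1 (pulmonary) and d2 (other variable) in the same direction, and within-arm correlation rw. The arms contribute d1·d2/4 to the covariance and d²/4 to each variance, so

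pooled r = (rw + d1·d2/4) / √[(1 + d1²/4)(1 + d2²/4)].

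**No within-arm correlation (rw = 0):**

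- d1 = d2 = 0.5: 0.0625 / 1.0625 = 0.06
- d1 = 1, d2 = 0.5: 0.125 / √(1.25 × 1.0625) = 0.125 / 1.152 = 0.11
- d1 = d2 = 1: 0.25 / 1.25 = 0.20
- d1 = 1, d2 = 0: 0

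**Real within-arm correlation (rw = 0.4), pulmonary shift only:** 0.4 / √1.25 = 0.36, so the coefficient is diluted.

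**Simulated Spearman tests.** Normal data, rw = 0, nominal 5%, 2,500 runs per case. The comparator uses ranks centred within arm.

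| Shifts (SD) | Mean pooled coefficient, n = 32 | Pooled test rejects, n = 32 | Pooled test rejects, n = 42 | Arm-centred test rejects, n = 32 / 42 |
|---|---|---|---|---|
| 1 and 0 | 0.00 | 4.3% | 4.8% | 4.4% / 5.0% |
| 0.5 and 0.5 | 0.06 | 6.1% | 5.8% | 4.8% / 5.2% |
| 1 and 0.5 | 0.10 | 8.2% | 10.6% | 4.3% / 5.4% |
| 1 and 1 | 0.21 | 20.9% | 26.4% | 5.3% / 5.1% |

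A separate simulation of 3,000 runs at n = 32, using the *t*-based 1.02 SD, gave 9.0% for 1.02 and 0.5 SD and 21.3% for 1.02 SD on both.

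**Dilution in the Spearman scale.** With rw = 0.4 and a 1 SD pulmonary shift only, the mean coefficient at n = 32 is 0.33, against 0.37 with no shift. The pooled test detects the association in 47% of runs and the arm-centred test in 55%.

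**The case against.** Several points on the other side are sound.

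- **Pooling is not stated.** It is the natural reading of a sentence that names no arm, in a condensed article whose analysis plan is not shown. The full plan may already handle arm. That limits the point to the method as written.
- **A successful trial does not by itself produce a false correlation.** A reader might infer that any benefit of EMT would do so. The documents do not support that. Section 1.4.4 judges efficacy on respiratory measures alone, and an effect confined to them creates no correlation with the other variable.
- **The bulbar effect is a question, not a firm hypothesis.** The Introduction's hypothesis covers respiratory measures. Speech and swallowing are to be assessed, and the Discussion says only that bulbar function may benefit. No text predicts an effect on disease progression rate.
- **The other variable may be a baseline value.** Section 1.3 uses bulbar impairment for a score that splits patients for stratification. If that score, or a progression rate fixed before randomisation, enters the correlation, it is independent of arm. The reference to longitudinal decline suggests change over time but does not settle it.
- **The 21% is an upper-end case.** It applies the FVC design effect to the bulbar side as well. At 0.5 SD on both sides the error rate is close to nominal.
- **No efficacy decision depends on it.** The between-group test is separate.

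Together these points make the matter minor. They do not remove it: the test as written has no way to account for arm, and the scenario in which that matters is one that the trial intends to test.

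**Conclusion.** The point holds as a minor improvement to a secondary analysis. As written, the Spearman test takes no account of arm, and a pooled coefficient would include a treatment component whenever EMT shifts both variables of a pair in the same direction. With no within-arm association, that component runs from about 0.06 (0.5 SD on both) to 0.20 (1 SD on both). The error rate at 32 patients runs from about 6% to 21%. The result rests on pooling, normal data, equal arms, a post-randomisation second variable, and assumed bulbar shifts.

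If only the pulmonary variable shifts, or the second variable is a baseline quantity, there is no false correlation, only mild dilution of a real one. A reader might also infer that the efficacy result is compromised. It is not, because the between-arm comparison does not use these correlations.

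**What to change.** Replace the Spearman sentence in section 1.6, or specify it in the analysis plan, as follows:

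> Spearman correlations between the decline rate of each pulmonary function test and (a) bulbar impairment and (b) disease progression rate will be computed as partial Spearman correlations adjusting for randomised arm, with arm-specific coefficients reported alongside.

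Add a statement of whether the bulbar and progression variables are baseline values or changes after randomisation, and define the progression rate. The adjusted coefficient is appropriate under either definition, so the choice need not wait for the results.

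The cost is this sentence, the added definitions and one degree of freedom. No new data or patients are needed.
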